#### Other Clinical Measures

In addition, the following clinical measures will be used to describe and compare the groups and considered as potential confounders:

1. Stroke subtype: Using the Oxfordshire Community Stroke Project (OCSP) Classification [47], a four item scale that classifies strokes using explicit criteria as either lacunar infarcts, total anterior circulation infarcts, partial anterior circulation infarcts, or posterior circulation infarcts.

2. Stroke severity: Using the Scandinavian Stroke Scale (SSS)[48], a measure of stroke severity involving assessment of the following parameters: consciousness, eye movement, motor power – arm, hand, leg, orientation, speech, facial palsy and gait to be measured on admission. Score range from zero to 58; the Los Angeles Motor Scale (LAMS), a motor deficit score ranging from zero (least affected) to ten (most affected) for bilateral weakness and zero to five in patients with unilateral weakness [49,50].

3. level of pre-morbid disability using the mRS [42,43]

4. demographic variables: age, sex, date of hospital admission, and length of stay

For missing data, patient clinical data will be obtained from the TASC database. Patients themselves will already have agreed to allow access to these data as part of the study consent. For hospitals that do not collect TASC data, stroke severity, stroke sub-type, level of pre-morbid mRS, and demographic variables will be prospectively manually collected from patient medical records by CRAs at each participating site following patient recruitment.

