**Figure 2 F2:**
[figure not shown]
**CONSORT Flow diagram of the progress through the phases of the trial (part 2) **[26].

After randomisation, the FeSS intervention will be implemented at those ASUs randomised to the intervention group. Following a minimum period of three months to allow the FeSS intervention to become an integral part of usual clinical practice in the intervention ASUs, a subsequent sample of patients will be recruited from all ASUs to provide post-intervention outcome data. These data will be collected using identical tools and methods to those used to collect baseline data. For the purpose only of temporal equity, each intervention ASU will be paired with a control ASU from the same category to calibrate the timing of post-intervention data collection.

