### Data Analyses

Blinded outcome assessment will be undertaken for all analyses of primary and secondary outcome measures. Data will be analysed using Stata [51]. Intention-to-treat analysis will applied [26].

To examine potential response bias, demographic characteristics for eligible consenting and non-consenting patients will be compared using the chi-square test for categorical variables (sex, stroke sub-type, and stroke severity) and the t-test (or a non-parametric equivalent) for the continuous variable of age.

For all patient-related outcome analyses, we will use cluster-specific methods. Dichotomous outcomes (death or disability [mRS ≥2] at 90 days; swallowing screen within 24 hours of admission) will be compared between intervention and control groups using the chi-square test. Continuous outcomes – level of disability (mRS score), dependency (Barthel Index), health status (MCS and PCS of SF-36), improved glycaemic control, and improved temperature control – will be compared between the two intervention groups using the t-test. The survey (svy) commands in Stata will be used to adjust for clustering of patients within ASUs. Multilevel modelling (logistic or linear as appropriate) will be used to compare primary outcomes – death or disability (mRS or ≥2) at 90 days, level of disability (mRS score), dependency (Barthel Index), and health status (MCS and PCS of SF-36) – between groups while adjusting for potential confounders or effect modifiers and for the cluster study design. These analyses will be undertaken in the Stata statistical package [51].

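### Length of stay, measured after allocation, is listed as a candidate confounder; if it enters the adjusted models of the primary outcomes, the treatment effect could be biased

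*Protocol article*

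**What the plan says.** In the protocol article, the section Other Clinical Measures opens by saying that "the following clinical measures will be used to describe and compare the groups and considered as potential confounders". Four groups of measures follow: stroke subtype, stroke severity, pre-morbid mRS, and "demographic variables: age, sex, date of hospital admission, and length of stay". Severity on the Scandinavian Stroke Scale is tied to admission, and the mRS in this list is pre-morbid. Length of stay has no such anchor.

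The Data Analyses section plans two layers of comparison:

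- Chi-square tests and t-tests, without covariates. "The survey (svy) commands in Stata will be used to adjust for clustering of patients within ASUs".
- Regression models. "Multilevel modelling (logistic or linear as appropriate) will be used to compare primary outcomes", and this is done "while adjusting for potential confounders or effect modifiers and for the cluster study design". The outcomes named are death or disability, mRS score, Barthel Index and the SF-36 component scores.

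No covariate is named in Data Analyses. Nothing there or elsewhere excludes length of stay or limits adjustment to variables fixed before the intervention can act.

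**The concern.** A confounder of a randomised comparison has to be related to allocation other than as its consequence. Length of stay can only be a consequence. It is also a plausible step between the intervention and the outcome, because fewer early complications may change how long a patient stays and how well the patient is at 90 days. It probably shares unmeasured causes with the outcome, such as frailty.

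Conditioning on such a variable can remove part of the effect that the trial is meant to estimate. It can also create an association where none exists, and randomisation does not protect against either. What is at stake is the only covariate-adjusted analysis of every primary outcome.

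**Working it through.** **The sections side by side**

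1. *Timing.* After allocation and at least three months of implementation, "a subsequent sample of patients will be recruited from all ASUs to provide post-intervention outcome data" (ASU randomisation, text after Figure 2). The whole stay of these patients therefore follows allocation.
2. *Possible mediation.* The behaviour-change outcomes cover the first 24 hours (swallowing screen) and the first 72 hours (temperature, glucose), so the intervention acts during the stay. The Background links swallowing dysfunction to aspiration, pneumonia and death.
3. *Outcome determining covariate.* Under Patient outcome measures, in-hospital deaths are counted in death or disability, and death scores 6 on the mRS. Death also ends the stay. For these two outcomes the outcome partly fixes the covariate. The article gives no death score for the Barthel Index or SF-36, so this step does not carry over to them.
4. *Link to the model.* Other Clinical Measures and Data Analyses both speak of potential confounders, so length of stay is a candidate for the models.

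**Size**

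The plan has no figure on this point to reproduce, and no data on stay, complication rates or the effect of the intervention on stay. The simulation below is illustrative, and every input is assumed. It has 1,000,000 patients per scenario, no clustering, and a binary outcome analysed by linear regression, so that effects are risk differences. Risk differences are used because a log-odds ratio shifts when a prognostic covariate is added, even without bias.

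A is randomised allocation, S measured severity and U an unmeasured cause. S and U are standard normal.

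- Complication C: logit = −1.0 + 0.5S + 0.5U + cA
- Poor outcome: logit = −1.3 + 0.8S + 1.0U + 1.0C + tA
- log(stay) = 2.0 + 0.3S + 0.4U + 0.5C + bA + error with SD 0.5
- With truncation: in-hospital death has logit −3.2 + S + U + 0.8C + tA, counts as poor outcome, and cuts stay to at most an exponential time with mean 5 days

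A value of b = ∓0.15 multiplies stay by 0.86 or 1.16 before any truncation; b = ∓0.3 multiplies it by 0.74 or 1.35.

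Estimated difference, intervention minus control, in percentage points:

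| Assumed scenario | Severity only | Plus stay in days | Plus log stay |
|---|---|---|---|
| Direct effect only (t = −0.5, c = 0, b = 0) | −7.34 | −7.32 | −7.32 |
| Same, with truncation | −8.01 | −8.31 | −8.12 |
| Direct effect, stay shortened (b = −0.15) | −7.39 | −5.35 | −4.65 |
| Direct effect, stay lengthened (b = 0.15) | −7.39 | −9.46 | −10.14 |
| Effect wholly through complications (t = 0, c = −2, b = 0) | −4.46 | −2.34 | −2.40 |
| Same, with truncation | −4.51 | −3.85 | −4.42 |
| No effect on outcome, stay shortened (b = −0.3), truncation | +0.10 | +2.00 | +0.87 |
| No effect on outcome, stay lengthened (b = 0.3), truncation | −0.03 | −1.71 | −0.20 |

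The Monte Carlo standard error of an entry is at most about 2 × √(0.36 × 0.64 / 1,000,000) = 0.001, or 0.1 points.

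In the wholly mediated case, adjusting for stay in days removes 1 − 2.34/4.46 = 48% of the effect without truncation and 1 − 3.85/4.51 = 15% with it. Where the intervention affects neither complications nor stay, almost nothing changes. A spurious 2 points can be set against the 12-point difference in the Sample Size section (35% versus 23%): 2/12 is about one sixth.

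**The case against.** Several points on the other side are sound:

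- The article says only that the measures are considered as potential confounders, and Data Analyses names no covariate. Length of stay is a candidate, not a fixed model term. The final covariate set is commonly left to an analysis plan, which is not at hand.
- Describing and comparing the groups by length of stay is legitimate.
- Every primary outcome is also compared without covariates. The article does not say that the multilevel model takes precedence.
- The size of any bias depends on assumed inputs. Truncation by death, which sounds as if it must make matters worse, reduced the loss in the wholly mediated scenario.
- With recruitment after allocation and few units, adjustment is reasonable, and stay might be defended as a proxy for severity. But severity on admission is already on the list and is not altered by the intervention.

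A reader might infer that the primary comparison would be biased, or that the effect would be diluted by a stated percentage. The documents support neither. Bias arises only if length of stay enters a model, it could run in either direction, and it could be negligible.

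These points limit certainty and size but do not remove the concern. Placing length of stay among potential confounders is a choice the article makes, not a detail it leaves open, and an analysis plan silent on the matter would inherit it. If covariates were chosen because the groups differ on them, stay would be picked when the intervention has changed it, which is when harm is most likely. The article states no selection rule that would prevent this.

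**Conclusion.** The concern holds in a conditional form. Length of stay is mislabelled as demographic and wrongly listed as a potential confounder: in the patients compared it follows allocation, may be a mediator, and is ended by a death that counts in two of the primary outcomes. If it is used for adjustment, the adjusted treatment effect on the primary outcomes could be biased, in a direction and by an amount the documents do not fix. The simulated figures show what is possible under assumed inputs and are not estimates for this trial. The chi-square and t-test comparisons with survey commands are untouched. This should be fixed, but it does not invalidate the plan.

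**What to change.** Remove length of stay from the candidate confounders in Other Clinical Measures, and keep it as a descriptive or outcome measure reported by group. State in Data Analyses that adjustment is restricted to variables fixed before ASU care: age, sex, pre-morbid mRS, stroke subtype, severity on admission and, if wanted, date of admission.

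The cost is one or two lines of text. No extra data or patients are needed, and the target of 520 per group stands, because its derivation uses no covariates (280 × 1.85 = 518, stated as 520).

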#### Professional behaviour change outcome measures

Changes in professional care also will be determined. Data will be obtained by retrospective medical record audit undertaken by independent research assistants (IRAs) blind to group allocation. A data dictionary will be developed and all research assistants will undergo training; inter-rater reliability testing will be undertaken (see 'behaviour change outcome measures' section for list of data to be collected).

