### Blinding

Both the medical director and NUM of all consenting ASUs will be aware that our study is examining the effect of an intervention to manage fever, hyperglycaemia and swallowing dysfunction following acute stroke. Furthermore, as control ASUs receive a minimum intervention, medical directors and NUMs from ASUs subsequently randomised to the control group may be able to deduce their group allocation because no workshops are being organised. However, all senior clinical members of control group ASUs remain blind to the exact nature of the intervention as described above.

CRAs recruiting patients will be blind at baseline to ASU group allocation. While some CRAs may infer group allocation at post-intervention data collection, they are responsible only for patient recruitment and not collection of outcome data *per se*. Patients will be blinded to group allocation. Data entry will be undertaken by the CATI research assistants blind to group allocation.

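### In hospitals without TASC data, site recruiters who may infer allocation also record the severity, subtype and pre-morbid mRS values considered for adjustment, so the covariate-adjusted estimates can be biased

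*Protocol article*

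**What the plan says.** Other Clinical Measures lists stroke subtype, stroke severity, pre-morbid mRS and demographics. These "will be used to describe and compare the groups and considered as potential confounders". Data Analyses then plans multilevel models that compare the primary outcomes "between groups while adjusting for potential confounders or effect modifiers and for the cluster study design".

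The covariates have two sources:

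- **TASC.** "For missing data, patient clinical data will be obtained from the TASC database". It is unclear whether TASC is the main source or only a back-fill.
- **Hand collection.** Where a hospital has no TASC data, the protocol says that these same items "will be prospectively manually collected from patient medical records by CRAs at each participating site following patient recruitment".

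The section on patient recruitment makes the CRAs the people in each acute stroke unit (ASU) who approach eligible patients. The document describes their role and blinding in three further places:

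- ASU randomisation calls them independent and blinded to all other parts of the design, without qualification.
- Blinding says they are blind at baseline but that some may infer allocation post-intervention. It discounts this because "they are responsible only for patient recruitment and not collection of outcome data"; the sentence ends with a qualifier limiting this to outcome data as such.
- Patient outcome measures asks them to report in-hospital deaths of enrolled patients.

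The professional-behaviour data come instead from a "retrospective medical record audit undertaken by independent research assistants (IRAs) blind to group allocation", supported by a data dictionary, training and inter-rater testing. No blinding is stated for the covariates that CRAs collect.

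**The concern.** The protocol's argument for tolerating CRA unblinding is that these staff only recruit. In hospitals without TASC they also fill in candidate adjustment variables for the primary outcomes. If a CRA knows the arm and scores severity accordingly, the two arms are no longer measured on the same scale. The adjusted model then treats a scoring difference as a real difference in case mix and corrects for it. Over-recorded severity in the intervention arm favours the intervention; under-recorded severity does the reverse.

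Only the post-intervention cohort is exposed, because ASUs are randomised after the baseline cohort's 90-day data are in.

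The point also touches the value of adjustment as a check. Post-intervention patients are recruited after allocation by staff who may infer it, so a severity-adjusted analysis is a natural safeguard against differential recruitment. That safeguard is weaker if the recruiter also records severity.

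**Working it through.** **1. The passages side by side.**

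| Question | Where | Statement |
|---|---|---|
| What do CRAs do? | Blinding | Recruitment only |
| | Other Clinical Measures | Abstract covariates in non-TASC hospitals |
| | Patient outcome measures | Notify in-hospital deaths |
| Are CRAs blind? | ASU randomisation | Yes, unqualified |
| | Blinding | At baseline yes; post-intervention some may infer |

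Both questions get conflicting answers.

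**2. Figures the document gives.** Sample Size states an mRS standard deviation of 2 and a target difference of 0.5. These agree with the hypothesis of 0.25 standard deviations: 0.5 / 2 = 0.25. Table 2 assumes nine units per group. The document gives no figure for the number of non-TASC units, for scoring error, or for the correlation of severity with outcome.

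**3. Formula.** In a linear model with no true effect, let r be the correlation of severity with 90-day mRS, d the shift in recorded severity (in standard deviations) at affected intervention units, and f the share of intervention units affected. Then

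bias in the adjusted mRS difference = −(r × 2) × d × f.

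**4. Main illustration (r, d and f assumed).** With f = 1/3 (three of nine units) and d = 0.1, the arm-wide shift is 0.1 / 3 = 0.033 standard deviations.

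- r = 0.5: 0.5 × 2 × 0.033 = 0.033, which is 7% of 0.5.
- r = 0.7: 0.7 × 2 × 0.033 = 0.047, which is 9% of 0.5.

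**5. Wider range (also assumed).** r from 0.3 to 0.6, d from 0.1 to 0.3, f from 1/3 to 2/3.

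- Smallest: 0.3 × 2 × 0.1 × 1/3 = 0.02 (4% of target).
- Largest: 0.6 × 2 × 0.3 × 2/3 = 0.24 (48% of target).

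A simulation used nine clusters per arm, 52 analysed patients per cluster, an ICC of 0.015, 1,000 runs per setting and a cluster-level t-test. It reproduced these biases closely. Type I error was 4.6% to 7.0% at d = 0.1, against 4.0% to 6.4% with no shift, and reached 23% at the largest setting. The unadjusted difference stayed centred on zero throughout.

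**6. TASC against hand abstraction.** Suppose 6 of 18 units are non-TASC (assumed) and are split at random nine to nine, ignoring strata. The split is 3:3 with probability 20 × 924 / 48,620 = 0.38, 4:2 either way with 2 × 15 × 792 / 48,620 = 0.49, and 5:1 or 6:0 either way with 2 × (2,970 + 220) / 48,620 = 0.13. The distribution is symmetric, so a source difference unrelated to arm has zero expected effect on the comparison. In a single 4:2 draw, a source difference of 0.3 standard deviations gives (4 − 2) / 9 × 0.3 = 0.067 standard deviations. With r of 0.5 to 0.7 that is 0.07 to 0.09 mRS, in either direction. This is chance imbalance between clusters, not systematic bias.

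**The case against.** The strongest reply has four parts.

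**The defence in Blinding concerns outcome data.** Severity, subtype and pre-morbid mRS are baseline covariates, and the 90-day interviews are done by blinded interviewers. This stands: only the claim that CRAs do nothing but recruit is contradicted, and outcome assessment by interview is untouched.

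**The adjusted models are not the only analysis.** Data Analyses also plans chi-square and t-test comparisons that allow for clustering but use no covariates. It does not list which potential confounders enter the models. This stands too. A reader might infer that every primary analysis is exposed, or that every listed covariate will certainly be used; the text supports neither.

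**The magnitude can easily be overstated.** A reader might apply a shift of 0.1 standard deviations to a whole arm and get 0.10 to 0.14 mRS, or 20 to 28% of the target. That would require scores to shift at every unit in the arm, whereas CRA abstraction is planned only where TASC is absent. Even the smaller figure assumes that all affected CRAs infer allocation and shift scores, while the document says only that some may infer it. It also uses a marginal correlation, and the coefficient in a model with several correlated covariates would be smaller.

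**The room for judgement is unknown.** Severity is to be measured on admission, and the subtype scale uses explicit criteria, so CRAs may merely transcribe recorded scores. The document does not say. Its statement that all research assistants are trained may or may not cover CRAs. This limits the size of the risk but does not remove the contradiction.

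**Conclusion.** The point holds as a conditional risk to the covariate-adjusted estimates in the post-intervention cohort, together with a plain inconsistency about what CRAs do and whether they are blinded. It requires recording that differs by arm; without that there is no bias by this route.

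Under the modest assumptions above (one-third of units affected, a 0.1 standard deviation shift, correlation 0.5 to 0.7), the adjusted mRS difference moves by 0.03 to 0.05, or 7 to 9% of the 0.5 target, with little effect on type I error. The upper end of 0.24 needs every assumption set unfavourably. None of these inputs comes from the document.

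A reader might also infer that using two data sources is itself a source of bias. It is not, because TASC use does not depend on allocation. TASC use is not a randomisation stratum, so an uneven split can occur by chance, but the consequence is mainly noise, residual confounding and between-unit variation, which models that account for clustering can largely reflect.

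**What to change.** - Have the blinded auditors abstract admission severity, subtype and pre-morbid mRS during the planned record audit, with the same data dictionary and inter-rater check at all sites and in both groups.
- Use these values in the adjusted models. Keep the TASC and CRA values as a cross-check.
- Reconcile ASU randomisation and Blinding with Patient outcome measures and Other Clinical Measures, so that the document gives one account of CRA tasks and one of CRA blinding.

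The cost is a few more fields and somewhat longer abstraction in an audit that already collects patient-level behaviour outcomes. The sponsor should confirm that the audit covers every analysed patient, which the article does not state outright. The change removes the unblinded abstractor but not any difference already written into the notes by ward staff who know their unit's allocation.

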#### Professional behaviour change outcome measures

Changes in professional care also will be determined. Data will be obtained by retrospective medical record audit undertaken by independent research assistants (IRAs) blind to group allocation. A data dictionary will be developed and all research assistants will undergo training; inter-rater reliability testing will be undertaken (see 'behaviour change outcome measures' section for list of data to be collected).

### Blinding

Both the medical director and NUM of all consenting ASUs will be aware that our study is examining the effect of an intervention to manage fever, hyperglycaemia and swallowing dysfunction following acute stroke. Furthermore, as control ASUs receive a minimum intervention, medical directors and NUMs from ASUs subsequently randomised to the control group may be able to deduce their group allocation because no workshops are being organised. However, all senior clinical members of control group ASUs remain blind to the exact nature of the intervention as described above.

CRAs recruiting patients will be blind at baseline to ASU group allocation. While some CRAs may infer group allocation at post-intervention data collection, they are responsible only for patient recruitment and not collection of outcome data *per se*. Patients will be blinded to group allocation. Data entry will be undertaken by the CATI research assistants blind to group allocation.

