#### Patient recruitment

##### Patient inclusion and exclusion criteria

To obtain baseline outcome and care data at the patient level, we will recruit a consecutive sample of English-speaking patients, aged >18 years, presenting within 48 hours of onset of symptoms who are given a clinical diagnosis of ischaemic stroke or intracerebral haemorrhage that is subsequently confirmed by CT imaging. These clinical criteria are specific and standard for stroke research. Patients will be excluded if they present to the ASU 48 hours or greater following onset of symptoms, have non-cerebrovascular causes of acute focal neurological deficits (seizure, hypoglycaemia, toxic or metabolic encephalopathies), sub-arachnoid haemorrhage, or acute and chronic subdural haemorrhage. Patients who require palliative care will not be approached.

All eligible patients will be approached by clinical research assistants (CRAs) identified in each ASU using a recruitment script. If an eligible patient agrees to participate in the study, they (or their family representative) will agree that researchers can contact them after 90 days of admission for a telephone interview; that researchers can access their medical records, and that TASC database can be accessed for their identified admissions data.

Our 90-day follow-up will comprise a computer-assisted telephone interview (CATI). One week prior to this CATI, a reminder letter will be mailed by the project officer (SD) to each participating patient. All CATIs will be undertaken by research interviewers blind to the study design and also to ASU group allocation [26,28]. These research interviewers all will have previous relevant experience and training in telephone administration of study measures. This CATI will include standard instruments as reported elsewhere in the section headed 'outcomes measures'.

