#### ASU randomisation

Once the baseline patient cohort 90-day outcome data have been collected, participating ASUs will be stratified and randomised. The project officer (SD) will first stratify ASUs according to their category classification (A or B) and then, by referring to absolute numbers of patients recruited at baseline, describe each as a 'high recruiter' or 'low recruiter'. Recruitment numbers will be included as a randomisation strata to maximise the chance of similar sample size in the intervention and control groups. Stratification details will be provided in a de-identified form to an independent statistician located offshore and not otherwise involved in the study for randomisation within strata, this will be generated using random number generating software[29]. Allocation will be based on clusters (ASUs) rather than individuals, and the sequence will be concealed until the intervention is assigned. Thus, generation of the allocation sequence and assigning of ASUs to either intervention or control group will be undertaken by the offshore independent statistician. To strengthen our methodological rigour, personnel who recruit patients (CRAs), research interviewers who undertake the CATIs, and the offshore statistician who undertakes randomisation all will be independent and also blinded to all other components of the study design. A flow diagram further outlining the trial design is shown in Figures 1 and 2.

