### Outcome measures

#### Patient outcome measures

1. Death or disability at 90 days post-hospital admission. Disability will be defined as a mRS of ≥ 2 [42,43]. Our CRAs at participating ASUs will be asked to inform us when patients enrolled in the study die while in hospital. Our letter to consenting patients one week prior to the CATI will enable relatives to contact the researchers to inform us of any patient death following discharge.

2. Level of disability at 90 days post-admission using the modified Rankin Score (mRS) [42,43], a six point measuring independence rather than performance of specific tasks. The scale ranges from zero to six, where zero corresponds with no symptoms, five corresponds to severe disability, and six corresponds with death. Disability will be defined as a mRS of ≥ 2 [42].

3. Level of dependency 90 days post-hospital admission using the Barthel Index (BI) [44]. The BI measures patient performance in 10 activities of daily life. The items are divided into groups that relate to self-care (feeding, grooming, bathing, dressing, bowel and bladder care, and toilet use) and a group related to mobility (ambulation, transfers, and stair climbing). The maximal score is 100 if five-point increments are used indicating the patient is fully independent in physical functioning. The lowest score is zero, representing a totally dependent bedridden state.

4. Health status 90 days post-hospital admission using the Medical Outcomes Study Short Form 36 Health Survey Questionnaire (SF-36) [45]. The SF-36 includes a single 'health transition rating' and scores eight health domains which are aggregated to form the Physical Component Score (PCS) and the Mental Component Score (MCS). Higher mean scores reflect better states of health and wellbeing [45]. This measure of self-perceived general health status is particularly sensitive to change between one to three months following stroke [46].

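### Recruiters who may infer allocation after randomisation also notify in-hospital deaths, so the article's blinding statements conflict and its defence leaves selection of patients never approached unanswered

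*Protocol article*

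**What the plan says.** Who recruits, and when:

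- *Patient inclusion and exclusion criteria*: "All eligible patients will be approached by clinical research assistants (CRAs) identified in each ASU using a recruitment script". The sampling rule is stated for baseline: "we will recruit a consecutive sample of English-speaking patients, aged >18 years, presenting within 48 hours of onset of symptoms". One group is left out before any approach: "Patients who require palliative care will not be approached".
- Text following Figure 2: after randomisation and at least three months of intervention, "a subsequent sample of patients will be recruited from all ASUs to provide post-intervention outcome data", using the same tools and methods as at baseline.

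What is said about blinding:

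- *ASU randomisation*: "personnel who recruit patients (CRAs), research interviewers who undertake the CATIs, and the offshore statistician who undertakes randomisation all will be independent and also blinded" (that is, with respect to the other parts of the study design).
- *Blinding*: CRAs are blind at baseline. For the later cohort, "While some CRAs may infer group allocation at post-intervention data collection, they are responsible only for patient recruitment and not collection of outcome data" (the sentence closes with *per se*).
- *Data Analyses*: outcome assessment is blinded for all primary and secondary outcomes.

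What else the CRAs do:

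- *Patient outcome measures*: "Our CRAs at participating ASUs will be asked to inform us when patients enrolled in the study die while in hospital".
- *Other Clinical Measures*: at hospitals that do not collect TASC data, CRAs extract stroke severity, subtype, pre-morbid mRS and demographics from the records.

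A blinded source already exists for the process outcomes (*Professional behaviour change outcome measures*): "Data will be obtained by retrospective medical record audit undertaken by independent research assistants (IRAs) blind to group allocation".

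**The concern.** The defence in the Blinding section has two parts, and neither holds fully. The first is that CRAs have no part in outcome data. They are the stated source for in-hospital deaths, which count towards death or disability (primary outcome 1) and score 6 on the mRS (primary outcome 2).

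The second is that recruitment is a harmless task for someone who may know the allocation. In a cluster trial that enrols patients after the clusters have been allocated, recruitment is the point at which the arms can come to differ. The palliative-care exclusion matters most here, because it is closely tied to death or disability and the article gives no criterion for it.

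If one arm approaches fewer very ill patients, or notifies deaths less completely, the arms differ on the primary outcome without any effect of the intervention.

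**Working it through.** **1. The statements side by side**

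| Topic | One place | Another place |
|---|---|---|
| CRA blinding | ASU randomisation: blinded | Blinding: blind at baseline; some may infer allocation later |
| CRA outcome role | Blinding: none | Patient outcome measures: notify in-hospital deaths |
| CRA task | Blinding: recruitment only | Other Clinical Measures: extract baseline covariates at non-TASC hospitals |
| Outcome assessment | Data Analyses: blinded for all primary outcomes | In-hospital deaths come through CRAs who may not be blind |

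The third row conflicts only with the claim that recruitment is the sole task. Severity, subtype and pre-morbid mRS are baseline covariates, not outcomes.

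**2. The plan's own sample size (Sample Size section and Table 2)**

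Inputs: 280 per group after 10% loss, nine units per group, ICC 0.015, 520 per group, control rate 35%.

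- Design effect: 1 + (520/9 − 1) × 0.015 = 1.85, as stated.
- 280 × 1.85 = 518, stated as 520.

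The point does not change the sample size.

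**3. Illustration of selection (assumed omissions)**

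Effective number per arm: 520 × 0.9 / 1.85 = 253. The true rate is 35% in both arms. The two-sided rejection rate is Φ(d/SE − 1.96) + Φ(−d/SE − 1.96), for a comparison adjusted for clustering but not for covariates.

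*(a) One arm omits a fraction f of eligible patients, all with poor outcomes.* The observed rate is (0.35 − f)/(1 − f).

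- f = 0.03: 0.32/0.97 = 33.0%, difference 2.0 points.
- f = 0.05: 0.30/0.95 = 31.6%, difference 3.4 points.
- SE = √(2 × 0.35 × 0.65 / 253) = 0.0424, giving rejection of 7.6% and 12.7%.
- With the design effect recalculated for 468 completers (52 per unit: 1 + 51 × 0.015 = 1.765; 468/1.765 = 265), SE = 0.0414 and rejection is 7.7% and 13.1%.

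These omissions amount to 0.03/0.35 = 8.6% and 0.05/0.35 = 14.3% of that arm's poor-outcome patients.

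*(b) One arm misses only 5% of its poor-outcome patients.*

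- Observed rate: 0.35 × 0.95 / (0.35 × 0.95 + 0.65) = 0.3325/0.9825 = 33.8%.
- Difference 1.2 points, rejection 5.9%.

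**4. Illustration of non-notified deaths (assumed)**

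Suppose in-hospital mortality m is 3% to 10%, and a share u of 10% to 50% goes unreported in one arm and is counted as lost. The observed rate is (0.35 − mu)/(1 − mu).

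- m = 3%, u = 10%: 0.347/0.997, bias 0.2 points.
- m = 10%, u = 50%: 0.30/0.95, bias 3.4 points.

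The upper end needs both extreme assumptions and no recovery of missed deaths at 90 days.

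**The case against.** The strongest reply is that the article discloses the possible unblinding and limits its consequences.

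- It says that some CRAs *may* infer allocation, not that all do.
- A reader might infer that recruiters choose who enters. The text does not support that: it prescribes a consecutive sample with every eligible patient approached by script, on criteria fixed by time window, age and CT-confirmed diagnosis. Nor does it say that the CRA decides who needs palliative care.
- A reader might also infer that nothing is compared between groups. In fact, Other Clinical Measures plans to compare the groups on subtype, severity, pre-morbid mRS and demographics, and Data Analyses plans multilevel models of the primary outcomes adjusted for potential confounders.
- A reader might infer that primary outcome assessment as a whole is unblinded. It is not: mRS, Barthel Index and SF-36 are obtained by blinded telephone interviewers. Death is objective, and a missed one may surface around the 90-day call. The relatives' letter is worded for deaths after discharge.
- The sizes rest on omission rates that the article does not give. Recruitment counts may be in the CONSORT figures, which are not shown.

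All of this stands and narrows the point. What remains is that the safeguards work on enrolled patients. The case-mix comparison and adjustment cannot see patients never approached, and the planned comparison of consenters with non-consenters covers only those asked and is not stated to be by group. At non-TASC hospitals, the adjustment covariates also pass through the CRAs. The closing *per se* softens the disclaimer of an outcome role, but does not reconcile it with the death-notification task.

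**Conclusion.** The concern holds in a limited form. The contradictions on CRA blinding and on their outcome role are in the text and need correcting. The argument that recruiters may safely infer allocation because they only recruit does not answer selection bias in a cohort enrolled after randomisation.

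Selection is the main risk. The ascertainment risk is differential non-notification of deaths, not misjudgement of them, and is smaller.

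No size can be established from the article. Under the assumed omissions, the spurious difference runs from 1.2 points (type I error about 6%) to 3.4 points (about 13%), before covariate adjustment, against a target difference of 12 points. The direction depends on which arm omits more. The documents give no evidence that such omission will occur.

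**What to change.** 1. Take in-hospital death for all post-intervention patients from the blinded record audit already planned. At hospitals without TASC data, take severity, subtype and pre-morbid mRS from the same audit. Patient consent already covers access to records.
2. Present the planned consenter versus non-consenter comparison by group, together with the number of patients not approached because of palliative care. A significance test of the group difference is not needed: with about 18 units it would have little power, and a null result would not exclude selection.
3. Reconcile ASU randomisation, Patient outcome measures, Blinding and Data Analyses, so that they say CRAs are not reliably blind after randomisation and name the source of each component of the primary outcome.

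The cost is a few added audit items, a count of patients not approached, and one table split by group. The comparison in Data Analyses already presupposes age, sex, subtype and severity for non-consenters, so the split by group needs no new patient variables. The sample size does not change.
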